| Adult and Pediatric > 14 days                                      | 1.1 – 1.5 x ULN                                                                                                    | 1.6 – 2.5 x ULN                                                                                                  | 2.6 – 5.0 x ULN                                                                                         | > 5.0 x ULN                                                                                   |
| Infant*†, ≤ 14 days
(non-hemolytic)                                | NA                                                                                                                 | 20.0 – 25.0 mg/dL
342 – 428 μmol/L                                                                     | 25.1 – 30.0 mg/dL
429 – 513 μmol/L                                                            | > 30.0 mg/dL
> 513.0 μmol/L                                                         |

| LABORATORY                                         |                                          |                                         |                                                                       |                                                                                                                      |
|----------------------------------------------------|------------------------------------------|-----------------------------------------|-----------------------------------------------------------------------|----------------------------------------------------------------------------------------------------------------------|
| PARAMETER                                          | GRADE 1
MILD                          | GRADE 2
MODERATE                     | GRADE 3
SEVERE                                                     | GRADE 4
POTENTIALLY
LIFE-THREATENING                                                                           |
| Infant*†, ≤ 14 days
(hemolytic)          | NA                                       | NA                                      | 20.0 – 25.0 mg/dL
342 – 428 μmol/L                                 | > 25.0 mg/dL
> 428 μmol/L                                                                                         |
| Calcium, serum, high (corrected for albumin)       |                                          |                                         |                                                                       |                                                                                                                      |
| Adult and Pediatric
≥ 7 days      | 10.6 – 11.5 mg/dL
2.65 – 2.88 mmol/L  | 11.6 – 12.5 mg/dL
2.89 – 3.13 mmol/L | 12.6 – 13.5 mg/dL
3.14 – 3.38 mmol/L                               | > 13.5 mg/dL
> 3.38 mmol/L                                                                                        |
| Infant*†, < 7 days                       | 11.5 – 12.4 mg/dL
2.88 – 3.10 mmol/L  | 12.5 – 12.9 mg/dL
3.11 – 3.23 mmol/L | 13.0 – 13.5 mg/dL
3.245 – 3.38 mmol/L                              | > 13.5 mg/dL
> 3.38 mmol/L                                                                                        |
| Calcium, serum, low (corrected for albumin)        |                                          |                                         |                                                                       |                                                                                                                      |
| Adult and Pediatric
≥ 7 days      | 7.8 – 8.4 mg/dL
1.95 – 2.10 mmol/L    | 7.0 – 7.7 mg/dL
1.75 – 1.94 mmol/L   | 6.1 – 6.9 mg/dL
1.53 – 1.74 mmol/L                                 | < 6.1 mg/dL
< 1.53 mmol/L                                                                                         |
| Infant*†, < 7 days                       | 6.5 – 7.5 mg/dL
1.63 – 1.88 mmol/L    | 6.0 – 6.4 mg/dL
1.50 – 1.62 mmol/L   | 5.50 – 5.90 mg/dL
1.38 – 1.51 mmol/L                               | < 5.50 mg/dL
< 1.38 mmol/L                                                                                        |
| Cardiac troponin I (cTnI)                          | NA                                       | NA                                      | NA                                                                    | Levels consistent with myocardial infarction or unstable angina as defined by the manufacturer                       |
| Cardiac troponin T (cTnT)                          | NA                                       | NA                                      | NA                                                                    | ≥ 0.20 ng/mL
OR
Levels consistent with myocardial infarction or unstable angina as defined by the manufacturer |
| Cholesterol (fasting)                              |                                          |                                         |                                                                       |                                                                                                                      |
| Adult ≥ 18 years                            | 200 – 239 mg/dL
5.18 – 6.19 mmol/L    | 240 – 300 mg/dL
6.20 – 7.77 mmol/L   | > 300 mg/dL
> 7.77 mmol/L                                          | NA                                                                                                                   |
| Pediatric < 18 years                     | 170 – 199 mg/dL
4.40 – 5.15 mmol/L    | 200 – 300 mg/dL
5.16 – 7.77 mmol/L   | > 300 mg/dL
> 7.77 mmol/L                                          | NA                                                                                                                   |
| Creatine Kinase                                    | 3.0 – 5.9 x ULN†                         | 6.0 – 9.9 x ULN†                        | 10.0 – 19.9 x ULN†                                                    | ≥ 20.0 x ULN†                                                                                                        |
| Creatinine                                         | 1.1 – 1.3 x ULN†                         | 1.4 – 1.8 x ULN†                        | 1.9 – 3.4 x ULN†                                                      | ≥ 3.5 x ULN†                                                                                                         |
| Glucose, serum, high                               |                                          |                                         |                                                                       |                                                                                                                      |
| Nonfasting                                         | 116 – 160 mg/dL
6.44 – 8.88 mmol/L    | 161 – 250 mg/dL
8.89 – 13.88 mmol/L  | 251 – 500 mg/dL
13.89 – 27.75 mmol/L                               | > 500 mg/dL
> 27.75 mmol/L                                                                                        |
| Fasting                                            | 110 – 125 mg/dL
6.11 – 6.94 mmol/L    | 126 – 250 mg/dL
6.95 – 13.88 mmol/L  | 251 – 500 mg/dL
13.89 – 27.75 mmol/L                               | > 500 mg/dL
> 27.75 mmol/L                                                                                        |
| Glucose, serum, low                                |                                          |                                         |                                                                       |                                                                                                                      |
| Adult and Pediatric
≥ 1 month     | 55 – 64 mg/dL
3.05 – 3.55 mmol/L      | 40 – 54 mg/dL
2.22 – 3.06 mmol/L     | 30 – 39 mg/dL
1.67 – 2.23 mmol/L                                   | < 30 mg/dL
< 1.67 mmol/L                                                                                          |
| Infant*†, < 1 month                      | 50 – 54 mg/dL
2.78 – 3.00 mmol/L      | 40 – 49 mg/dL
2.22 – 2.77 mmol/L     | 30 – 39 mg/dL
1.67 – 2.21 mmol/L                                   | < 30 mg/dL
< 1.67 mmol/L                                                                                          |
| Lactate                                            | < 2.0 x ULN without acidosis             | ≥ 2.0 x ULN without acidosis            | Increased lactate with pH < 7.3 without life-threatening consequences | Increased lactate with pH < 7.3 with life-threatening consequences                                                   |
| LDL cholesterol (fasting)                          |                                          |                                         |                                                                       |                                                                                                                      |
| Adult ≥ 18 years                            | 130 – 159 mg/dL
3.37 – 4.12 mmol/L    | 160 – 190 mg/dL
4.13 – 4.90 mmol/L   | ≥ 190 mg/dL
≥ 4.91 mmol/L                                          | NA                                                                                                                   |
| Pediatric > 2 - < 18 years            | 110 – 129 mg/dL
2.85 – 3.34 mmol/L    | 130 – 189 mg/dL
3.35 – 4.90 mmol/L   | ≥ 190 mg/dL
≥ 4.91 mmol/L                                          | NA                                                                                                                   |
| Lipase                                             | 1.1 – 1.5 x ULN                          | 1.6 – 3.0 x ULN                         | 3.1 – 5.0 x ULN                                                       | > 5.0 x ULN                                                                                                          |
| Magnesium, serum, low                              | 1.2 – 1.4 mEq/L
0.60 – 0.70 mmol/L    | 0.9 – 1.1 mEq/L
0.45 – 0.59 mmol/L   | 0.6 – 0.8 mEq/L
0.30 – 0.44 mmol/L                                 | < 0.60 mEq/L
< 0.30 mmol/L                                                                                        |
| Pancreatic amylase                                 | 1.1 – 1.5 x ULN                          | 1.6 – 2.0 x ULN                         | 2.1 – 5.0 x ULN                                                       | > 5.0 x ULN                                                                                                          |
| Phosphate, serum, low                              |                                          |                                         |                                                                       |                                                                                                                      |
| Adult and Pediatric
> 14 years | 2.5 mg/dL – < LLN
0.81 mmol/L – < LLN | 2.0 – 2.4 mg/dL
0.65 – 0.80 mmol/L   | 1.0 – 1.9 mg/dL
0.32 – 0.64 mmol/L                                 | < 1.00 mg/dL
< 0.32 mmol/L                                                                                        |
| Pediatric 1 year – 14 years                 | 3.0 – 3.5 mg/dL
0.97 – 1.13 mmol/L    | 2.5 – 2.9 mg/dL
0.81 – 0.96 mmol/L   | 1.5 – 2.4 mg/dL
0.48 – 0.80 mmol/L                                 | < 1.50 mg/dL
< 0.48 mmol/L                                                                                        |
| Pediatric < 1 year                       | 3.5 – 4.5 mg/dL
1.13 – 1.45 mmol/L    | 2.5 – 3.4 mg/dL
0.81 – 1.12 mmol/L   | 1.5 – 2.4 mg/dL
0.48 – 0.80 mmol/L                                 | < 1.50 mg/dL
< 0.48 mmol/L                                                                                        |
| Potassium, serum, high                             | 5.6 – 6.0 mEq/L
5.6 – 6.0 mmol/L      | 6.1 – 6.5 mEq/L
6.1 – 6.5 mmol/L     | 6.6 – 7.0 mEq/L
6.6 – 7.0 mmol/L                                   | > 7.0 mEq/L
> 7.0 mmol/L                                                                                          |
| Potassium, serum, low                              | 3.0 – 3.4 mEq/L
3.0 – 3.4 mmol/L      | 2.5 – 2.9 mEq/L
2.5 – 2.9 mmol/L     | 2.0 – 2.4 mEq/L
2.0 – 2.4 mmol/L                                   | < 2.0 mEq/L
< 2.0 mmol/L                                                                                          |

| LABORATORY                                                                     |                                                               |                                                               |                                                                 |                                                          |
|--------------------------------------------------------------------------------|---------------------------------------------------------------|---------------------------------------------------------------|-----------------------------------------------------------------|----------------------------------------------------------|
| PARAMETER                                                                      | GRADE 1
MILD                                               | GRADE 2
MODERATE                                           | GRADE 3
SEVERE                                               | GRADE 4
POTENTIALLY
LIFE-THREATENING               |
| Sodium, serum, high                                                            | 146 – 150 mEq/L
146 – 150 mmol/L                    | 151 – 154 mEq/L
151 – 154 mmol/L                    | 155 – 159 mEq/L
155 – 159 mmol/L                      | ≥ 160 mEq/L
≥ 160 mmol/L                       |
| Sodium, serum, low                                                             | 130 – 135 mEq/L
130 – 135 mmol/L                    | 125 – 129 mEq/L
125 – 129 mmol/L                    | 121 – 124 mEq/L
121 – 124 mmol/L                      | ≤ 120 mEq/L
≤ 120 mmol/L                       |
| Triglycerides (fasting)                                                        | NA                                                            | 500 – 750 mg/dL
5.65 – 8.48 mmol/L                  | 751 – 1,200 mg/dL
8.49 – 13.56 mmol/L                 | > 1,200 mg/dL
> 13.56 mmol/L                |
| Uric acid                                                                      | 7.5 – 10.0 mg/dL
0.45 – 0.59 mmol/L                 | 10.1 – 12.0 mg/dL
0.60 – 0.71 mmol/L                | 12.1 – 15.0 mg/dL
0.72 – 0.89 mmol/L                  | > 15.0 mg/dL
> 0.89 mmol/L                  |
| URINALYSIS
Standard International Units are listed in italics |                                                               |                                                               |                                                                 |                                                          |
| Hematuria (microscopic)                                                        | 6 – 10 RBC/HPF                                                | > 10 RBC/HPF                                                  | Gross, with or without clots OR with RBC casts                  | Transfusion indicated                                    |
| Proteinuria, random collection                                                 | 1 +                                                           | 2 – 3 +                                                       | 4 +                                                             | NA                                                       |
| Proteinuria, 24 hour collection                                                |                                                               |                                                               |                                                                 |                                                          |
| Adult and Pediatric ≥ 10 years                                          | 200 – 999 mg/24 h
0.200 – 0.999 g/d                 | 1,000 – 1,999 mg/24 h
1.000 – 1.999 g/d             | 2,000 – 3,500 mg/24 h
2.000 – 3.500 g/d               | > 3,500 mg/24 h
> 3.500 g/d                 |
| Pediatric > 3 mo - < 10 years                                     | 201 – 499 mg/m  /24 h
0.201 – 0.499 g/d | 500 – 799 mg/m  /24 h
0.500 – 0.799 g/d | 800 – 1,000 mg/m  /24 h
0.800 – 1.000 g/d | > 1,000 mg/m  /24 h
> 1.000 g/d |

\* Values are for term infants.

† Use age and sex appropriate values (e.g., bilirubin), including preterm infants.

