**1.1.6 Data recorded directly on CRFs**

Clinical and routine laboratory data will be recorded on case report forms (CRFs). A copy will be faxed or sent to the MRC CTU for data entry and the original will be kept at the local centre. For more details see section 7.

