## 7.3 Procedures for assessing safety

A symptom evaluation and targeted physical examination will be performed at each visit.

Body composition changes will be evaluated at baseline, annual visits and the final study visit as follows:

- Waist circumference will be measured between the lower border of the ribs and the iliac crest, in a horizontal plane.
- Hip circumference will be measured at the widest point over the buttocks.
- Patients will be asked about any change in fat in the face, arms, legs or abdomen. Taking into account the patient's opinion, the research nurse or doctor will grade facial lipoatrophy as none, moderate (evident on inspection), or severe (immediately obvious).

Patients will be asked about symptoms of peripheral neuropathy at baseline, annual visits and the final study visit. A brief neuropathy examination will be performed at baseline and the final study visit in all patients, and at intervening annual study visits if the patient reports neuropathy symptoms

Cardiovascular risk factors will be assessed at annual trial visits, and risk will be quantified using the Joint British Societies cardiovascular risk prediction charts (see Appendix 11).

Blood will be drawn at trial visits to assess laboratory safety parameters according to standard-of-care as indicated in the schedule of trial assessments (see section 1.3). Additional safety blood tests or investigations will be performed to investigate symptoms or monitor emergent laboratory test abnormalities as clinically indicated.

All adverse events will be reported on the case report form. Adverse events (clinical and laboratory) will be graded using the 2004 Division of AIDS toxicity grading scale (see Appendix 7). Serious adverse events will be defined according to the EU Directive 2001/20/EC Article 2 based on ICH GCP, and will be reported to the MRC CTU for the duration of the main trial i.e. whilst patients are attending trial visits according to standard timelines (see section 11).

Diagnostic criteria for selected serious AIDS and non-AIDS events are defined in the protocol (see section 9.2.2 and Appendices 8 and 9), and sites will be encouraged to investigate patients in a way that allows determination of whether patients meet the specified diagnostic criteria. An independent endpoint review committee will review these endpoints to ensure that they satisfy the criteria.

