#### 9.2.2 Secondary outcome measures

- **Serious drug or disease-related complication**

Defined as the first occurrence of one of the following in any individual patient:

- **Death from any cause**
- **Serious AIDS-defining illness** (see diagnostic criteria, Appendix 7)
- **Serious non-AIDS defining illness** (see diagnostic criteria, Appendix 8)
  - Acute myocardial infarction
  - Coronary artery disease requiring invasive procedures
  - Cirrhosis
  - Acute liver failure
  - End-stage renal disease
  - Stroke
  - Clinical acute pancreatitis
  - Severe lactic acidemia
  - Severe facial lipoatrophy
  - Severe peripheral neuropathy
  - Non-AIDS malignancy

- **Adverse events**

Defined as the total number of Grade III and IV adverse events.

- **Confirmed Virological rebound**

Defined as 3 consecutive VL tests  $\geq 50$  copies/ml, with at least 4 weeks between the first and last test. One of these 3 tests may be a repeat of the same sample. There are a number of alternative definitions for virological rebound, each of which has advantages and limitations (28). The alternative definitions to be used in this trial will be described in the full statistical analysis plan.

- **CD4+ count change**  
Defined as change from baseline in absolute CD4+ count.
- **Health-related Quality of Life change**  
Defined as change from baseline in the mental and physical health summary scores.
- **Neurocognitive function change**  
Defined as change from baseline in the neurocognitive function summary score.
- **Cardiovascular risk change**  
Defined as change from baseline in the risk of cardiovascular disease calculated from the Framingham equation (19).
- **Health care costs**  
Defined as the total cost of health care resources utilised per patient year.

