### 9.5.2 Secondary analyses

The primary analysis will be extended to tabulate individual ART drug options and ART class options which are lost due to the development of resistance. Time-to-event methods will be used to analyse the rate of serious drug- or disease-related complications and for viral load rebound. Also, the frequency of grade III and IV adverse events will be tabulated by body systems and randomised group and the groups will be compared using the  $\chi^2$  test. Repeated measures analysis will be used to compare change in CD4+ cell count from baseline in the allocated strategies.

Patient responses on the MOS-HIV questionnaire will be converted to scores on 11 subscales, ranging from 0 to 100, with higher scores indicating better health (32). The scores are then synthesised into a physical health summary score (PHS) and a mental health summary score (MHS). A general linear mixed model will be used to compare the two groups in terms of changes from baseline in the summary PHS and MHS quality of life indexes over the follow-up period.

The scores on each of the neurocognitive tests will be standardised using demographic-adjusted normative means. This procedure will adjust the data for gender, age, level of education and ethnic background. Briefly, standard scores will be calculated by subtracting the appropriate normative mean from the raw score and then dividing by the appropriate normative standard deviation to give a z score (33). The patient's individual z scores on each test will be averaged to give the patient's neurocognitive function summary score at each

visit. A general linear mixed model will be used to compare the two groups in terms of changes from baseline in the neurocognitive function summary score.

Changes from baseline in the 10-year cardiovascular risk score will also be compared between the two groups using a general linear mixed model.

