### 10.3 Clinical site monitoring

On-site monitoring will be conducted at all sites at a frequency of approximately one visit per year. The first monitoring visit for each site will be performed after 4-6 patients have been randomised or at 6 months following the date the site randomised its first patient, whichever occurs first. The CRFs of all patients enrolled will be reviewed at the first monitoring visit. For high-recruiting sites, a sample of no less than 5 patients will be selected by the MRC CTU for review at subsequent visits. Priority will be given to selecting patients for whom the CRFs have not been previously monitored.

Scheduling of subsequent visits will be performed using a risk based approach.

MRC monitors will:

- verify completeness of Trial Master File
- confirm adherence to protocol
- review eligibility verification and consent procedures
- look for missed event reporting
- verify completeness, consistency and accuracy of data being entered on CRFs
- provide additional training as needed

The monitors will require access to all patient medical records including, but not limited to, laboratory test results and prescriptions. The investigator (or delegated deputy) should work with the monitor to ensure that any problems detected are resolved.

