#### (d) Notification

***Please also refer to the safety reporting flowchart on the following page***

All AEs/ARs, whether expected or not, should be graded using the toxicity table in Appendix 6 and should be then recorded in the toxicity (symptoms) section of the appropriate visit CRF. If the event is grade 3, 4 or an SAE an Event CRF should be completed. This should be sent to the MRC CTU within one working day of the site becoming aware of the SAE or within one month of the grade 3 or 4 event. .

Adverse drug reactions to licensed PIs will continue to be reported by the investigator to the Yellow Card Scheme run by the MHRA and Commission on Human Medicines.

Investigators should record all SAEs occurring from the time of randomisation until 30 days after the last trial visit.

A Safety Reporting Flowchart (Figure 2) is given at the end of this section to help explain the classification and reporting of events. Any questions concerning this process should be directed to the MRC CTU in the first instance. The notification procedure is as follows:

1. The Event CRF must be completed by the investigator (clinician named on the Delegation of Authority log who is responsible for the patient's care), with due care being paid to the grading, causality and expectedness of the event as outlined above. In the absence of the responsible investigator, the form should be completed and signed by a member of the site trial team. The responsible investigator should subsequently check the Event CRF, make changes as appropriate, sign and then re-fax to the MRC CTU as soon as possible. The initial report shall be followed by detailed, written reports as appropriate.
2. Send the Event CRF by fax to the MRC CTU, fax number: [name].
3. Follow-up: Patients must be followed-up until clinical recovery is complete and laboratory results have returned to normal or baseline, or until the event has stabilised. Follow-up should continue after completion of protocol treatment if necessary. Follow-up information for the event should be noted on a new Event CRF by ticking the box marked 'follow-up' and faxing to the MRC CTU as information becomes available. Extra, annotated information and/or copies of test results may be provided separately. The patient must be identified by trial number, date of birth and initials only. The patient's name should not be used on any correspondence. A new Event CRF should be completed for the final report.

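### The only route described for laboratory Grade III/IV events is grading by the unblinded site; deriving them by program from the recorded values would be a cheap improvement

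*Combined protocol and SAP*

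**What the plan says.** Section 1.1.1 describes an open-label trial, and the second objective in section 2.4.1 is to compare safety and toxicity.

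- **Scope.** Section 7.3: "Adverse events (clinical and laboratory) will be graded using the 2004 Division of AIDS toxicity grading scale". The scale is reproduced in Appendix 6, where "LDL cholesterol (fasting" is one of the laboratory rows.
- **Route.** Section 11.2.1(d), under investigator responsibilities: "All AEs/ARs, whether expected or not, should be graded using the toxicity table in Appendix 6 and should be then recorded", the place of recording being the toxicity (symptoms) section of the visit CRF. Then: "If the event is grade 3, 4 or an SAE an Event CRF should be completed".
- **Outcome.** Section 9.2.2: "Defined as the total number of Grade III and IV adverse events". No data source is named, and laboratory and clinical events are not split.
- **Analysis.** Section 9.5.2: "the frequency of grade III and IV adverse events will be tabulated by body systems and randomised group", followed by a chi-squared comparison.
- **Values held centrally.** Section 1.1.6: "Clinical and routine laboratory data will be recorded on case report forms (CRFs", with a copy sent to the trials unit. Section 10.4 adds faxed laboratory reports where possible.

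**The concern.** The laboratory rows of Appendix 6 are mostly numeric cut-offs. Once the value is known, the grade needs no judgement. Yet the described route passes through staff who know the allocation, and it uses a CRF section headed for symptoms. A symptomatic event prompts a report by itself. An asymptomatic LDL or ALT result does so only if someone at the site compares it with the table and treats it as an adverse event.

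If sites do this more readily in one arm, the reported totals could differ with no true difference behind them, or a true difference could be narrowed. Either direction is possible. Sites may watch the new strategy more closely, or may look harder for known toxicity of the control drugs.

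**Working it through.** The plan gives no rate, effect size, power or significance level for this comparison, so there is no stated figure to reproduce. The check has two parts: tracing the route, and showing what unequal capture could do under assumed rates.

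**1. Is there a central step that would pick up an unreported Grade 3 or 4 value?**

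| Section | What it covers | Grades recorded laboratory values? |
|---|---|---|
| 10.2 | Checks for missing or unusual values and for consistency, with queries to sites | No grading rule described |
| 10.3 | Monitoring at all sites about once a year, with missed events among the tasks | Retrieves some missed reports; sampling allowed later at high-recruiting sites |
| 11.3 | Medical review of event reports received | No; needs a report first |
| 16.4 | Committee review of serious drug or disease-related events | No; a different outcome |

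The sampling rule is "For high-recruiting sites, a sample of no less than 5 patients will be selected by the MRC CTU for review at subsequent visits". With 560 patients at about 50 sites (sections 1.1.2 and 3), the average is 560/50 = 11.2 patients per site.

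**2. How many values are involved?** With uniform accrual over 24 of 60 months (section 9.3), mean follow-up is 60 − 24/2 = 48 months, or 17 twelve-weekly visits (to week 204). Twelve of these carry 10 gradeable results: haemoglobin, white cells, neutrophils, platelets, sodium, potassium, creatinine, bilirubin, ALT and alkaline phosphatase. Five (week 12 and four annual visits) carry 16, adding calcium, phosphate, glucose, cholesterol, LDL and triglycerides. Total: 12 × 10 + 5 × 16 = 200 per patient, ignoring losses and a separate final visit. The Week 4 visit adds 14 more (10 plus glucose and three lipids) in the PI monotherapy arm only.

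**3. Illustration: unequal reporting.** Assume n = 280 per arm, a two-sided 5% test, the same true risk π in both arms of at least one Grade III/IV laboratory value, and one chance of reporting per affected patient with probability r₁ (PI) or r₂ (control). Then p₁ = πr₁, p₂ = πr₂, d = p₁ − p₂ and p̄ = (p₁ + p₂)/2. With s₀ = √[2p̄(1 − p̄)/n] and s₁ = √{[p₁(1 − p₁) + p₂(1 − p₂)]/n},

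P(reject) ≈ Φ[(|d| − 1.96s₀)/s₁] + Φ[(−|d| − 1.96s₀)/s₁].

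For π = 0.20, r₁ = 0.90 and r₂ = 0.70: p₁ = 0.18, p₂ = 0.14, s₀ = 0.0310 and s₁ = 0.0309. The first term is Φ(−0.67) = 0.251 and the second is about 0.001, so P = 0.252.

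| True risk | 90% v 70% | 90% v 80% |
|---|---|---|
| 10% | 14% | 7% |
| 20% | 25% | 10% |
| 30% | 38% | 13% |

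**4. How far does this depend on one chance per patient?** If each affected patient has three abnormal values, each reported independently, capture is 1 − 0.1³ = 99.9% against 1 − 0.3³ = 97.3%. At π = 0.20 the reported rates are 20.0% and 19.5%, and the test rejects 5.3% of the time. The inflation almost disappears.

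**5. Illustration: one total.** Assume laboratory events in 11% (control) v 19% (PI), clinical events in 29% v 21%, and independence. Any event: 1 − 0.89 × 0.71 = 36.8% v 1 − 0.81 × 0.79 = 36.0%. Power is 76% for laboratory alone, 59% for clinical alone, and 5% combined.

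Steps 3 to 5 count patients with at least one event, which suits a chi-squared test. Section 9.2.2 speaks of the number of events.

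**The case against.** The strongest reply is that section 11.2.1(d) is a notification procedure and not an analysis rule. It requires every event to be graded, so omitting a Grade 3 laboratory value would be non-compliance and not permitted discretion. The values are held centrally, are range-checked, and can be graded at any time. Section 9.5 is only a summary, with a full analysis plan to follow.

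Much of this stands. A reader might infer that a laboratory abnormality counts only if the site files an Event CRF. The documents do not say so, because section 9.2.2 names no data source. A reader might also infer that combining the events conceals opposing effects. The planned body-system table would show such shifts at least descriptively, and lipids also enter the separate cardiovascular risk outcome without any adverse event report. Separate tests are largely a matter of presentation.

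What remains is that a compliance requirement does not make capture equal between arms, and that the unit holds the values without any stated plan to grade them. Deferral to a later analysis plan means the point can still be settled; it does not settle it.

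**Conclusion.** The point holds as a worthwhile, inexpensive improvement. Laboratory Grade III/IV events belong to the outcome, the only grading and reporting route described is the unblinded site, and no central grading of recorded values is specified. Capture of asymptomatic abnormalities could therefore differ by arm.

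The size and direction of any bias cannot be determined from the documents. The rejection rates of 7% to 38% should not be read as estimates for this trial. They rest on assumed risks and assumed reporting rates, and fall to about 5% when three abnormal values per affected patient are each reported independently. The combined-total example likewise shows what could happen under assumed opposing shifts. The recommendation rests mainly on programmed grading; the separate lines are a helpful addition.

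**What to change.** In sections 9.2.2 and 9.5.2, and in the full analysis plan:

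1. Derive laboratory Grade III/IV events by program from the values on the visit CRFs, using the Appendix 6 thresholds and each local laboratory's upper limit of normal where a threshold needs one. Do this identically in both arms, whether or not an Event CRF was filed.
2. Show laboratory and clinical Grade III/IV events on separate lines beside the combined total, in addition to the planned body-system table.

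The program specification should settle a few details. The calcium rows are albumin-corrected, but albumin is not among the listed tests. The adult LDL grades meet at 190 mg/dL but are distinct in mmol/L. Programmed grading does not remove the extra Week 4 sample in the PI arm, so a rerun without that visit would be a simple check.

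The cost is analysis-plan wording, programming, and collecting local upper limits for ALT, alkaline phosphatase, bilirubin and creatinine. The derived count will not match the Event CRF listing exactly, and the report should say why. Patient care and visits do not change.
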